## Abstract

**Purpose:**

The role of supplemental artificial nutrition in patients perioperatively treated according to enhanced recovery programs (ERAS) on surgery-related morbidity is not known. Therefore, there is a need of a clinical trials specifically designed to explore whether given a full nutritional requirement by parenteral feeding after surgery coupled with oral food “at will” compared to oral food “at will” alone, within an established ERAS program, could achieve a reduction of the morbidity burden.

**Materials and analysis:**

RASTA will be a multicenter, randomized, parallel-arm, open labeled, superiority trial. The trial will be conducted in five Italian Institutions with proven experience in pancreatic surgery and already applying an established ERAS program. Adult patients (age ≥ 18 and < 90 years of age) candidate to elective open pancreatoduodenectomy (PD) for any periampullary or pancreatic cancer will be randomized to receive a full ERAS protocol that establishes oral food “at will” plus parenteral nutrition (PN) from postoperative day 1 to day 5 (treatment arm), or to ERAS protocol without PN (control arm). The primary endpoint of the trial is the complication burden within 90 days after the day of surgery. The complication burden will be assessed by the Comprehensive Complication Index, that incorporates all complications and their severity as defined by the Clavien-Dindo classification, and summarizes postoperative morbidity with a numerical scale ranging from 0 to 100. The H0 hypothesis tested is that he administration of a parenteral nutrition added to the ERAS protocol will not affect the CCI as compared to standard of care (ERAS). The H1 hypothesis is that the administration of a parenteral nutrition added to the ERAS protocol will positively affect the CCI as compared to standard of care (ERAS). The trial has been registered at ClinicalTrials.gov (number: NCT04438447; date: 18/05/2020).

**Conclusion:**

This upcoming trial will permit to establish if early postoperative artificial nutritional support after PD may improve postoperative outcomes compared to oral nutrition alone within an established ERAS program.

## Introduction

The enhanced recovery after surgery (ERAS) program is currently considered the gold-standard pathway for perioperative care in many types of operations (1) including pancreatoduodenectomy (PD) (2). The protocol is a bundle of interventions derived from the best evidence-based perioperative treatments aimed to accelerate patient functional recovery through the reduction of dysmetabolism and dyshomeostasis caused by surgery- and anesthesiology-related injury. In general, the implementation of ERAS generates a reduction of surgery-related complication, duration of hospitalization, and health care-related costs (1).

The intake of adequate qualitative and quantitative nutritional substrates is needed for appropriate tissue healing and recovery/maintenance of organ function after major surgery. To recover gut function and tolerate early postoperative oral feeding, many ERAS elements need to be implemented as they act in synergy (3).

PD is one of the most complex and challenging abdominal operations with a high rate of morbidity (4) and significant catabolic consequences. Moreover, the proportion of patients undergoing PD for cancer are at high nutritional risk or suffer some nutritional derangements at baseline in up to 80% of the cases (5). In addition, delayed gastric emptying (DGE) after PD is frequent (up to 50%) (6) compromising the regular resumption of oral food with the risk of developing postoperative malnutrition.

According to expert opinions (7), artificial nutritional support should be implemented early postoperatively in malnourished patients, in those patients at high risk of developing malnutrition, in those who develop complications affecting oral feeding tolerance, and in well-nourished patients who do not tolerate at least 50% of their caloric and protein requirement by postoperative day 7 for any reason. Accordingly, most of the patients bearing pancreatic cancer and undergoing PD should receive some form of artificial nutritional support after the operation. Conversely, ERAS pathways promote oral food “at will” early after surgery and consider an artificial nutritional support only in selected cases (8). Furthermore, there are no convincing data on whether attaining adequate nutritional needs can be accomplished only by progressive increase of oral food intake. A study reported (9) that, the mean daily calorie and protein intake in the first 2 weeks were similar between the ERAS group and the patients managed conventionally. Anyhow, the results revealed that the total energy goal through oral feeding was not reached in both groups. Other studies did not analyze or reported incomplete data on tolerance to early postoperative oral feeding (EOF) after PD (10, 11). Robertson et al. (12) described compliance rates of 82% for resumption of oral fluids and 86% for tolerance of solid diet. Conversely, in another large study (13), postoperative oral liquids were tolerated by 55% of the patients and solid food in 53%, but compliance dropped substantially in patients with a complicated postoperative course. Thus, the available evidence suggests that using only oral feeding (food “at will”) within an ERAS protocol may be only partially adequate to achieve the nutritional needs after PD.

Given the lack of strong evidence, there is a need for a randomized clinical trial specifically designed to explore the extent to which reaching full nutritional requirements by adding parenteral feeding in the first days after surgery within an established ERAS program impacts on postoperative morbidity compared to oral food “at will” alone.

## Study design and management

RASTA will be a multicenter, randomized, parallel-arm, open labeled, superiority trial.

The trial will be conducted in five Italian Institutions with proven experience in pancreatic surgery and an established ERAS program.

THE RASTA trial will be managed and coordinated by the School of Medicine and Surgery of the Milano-Bicocca University and the HPB Unit of the IRCCS San Gerardo Hospital, Monza, Italy. The coordinating center will also be responsible for treatment allocation and monitoring, and statistical analysis with the support of the Centre of Biostatistics for Clinical Epidemiology of the Milano-Bicocca University.

The trial has been registered at ClinicalTrials.gov (ID: NCT04438447; date: June 16, 2020) and approved by the Italian Drug Agency (AIFA; number: EudraCT 2020–005483-66; date: September 13, 2021).

### Pre-trial training

Before starting patient enrolment, multiple meetings will be organized to accomplish:

- Correct definition of eligibility, inclusion and exclusion criteria.- Agreement on definition of postoperative complications.- Training on randomization process and patient instruction on treatment arms.- Accordance on ERAS elements (described in Table 1).- Training of outcome assessors to record the occurrence of the primary and secondary endpoints. Each participating center will nominate two independent outcome assessors. The assessors will be trained by the single center principal investigator on the definition of complications during a dedicated pre-trial face-to-face meeting according to a modified Delphi method. In case of discordance on the assignment of the endpoint, a third expert will intervene to solve the dispute and classify the patients as complicated or not. Outcome assessors will be blinded to treatments.- Training on how to fill out correctly the case report form.

**Table 1 tab1:** ERAS items implemented in both groups.

Item	Yes	No
Preoperative counseling	X	
Prehabilitation		X
Preoperative biliary drainage		X
Preoperative stop of smoking and alcohol consumption	X	
Preoperative nutrition		X
Perioperative oral immunonutrition		X
Preoperative fasting		X
Preoperative carbohydrate loading	X	
Pre-anesthetic medication		X
Anti-thrombotic prophylaxis	X	
Antimicrobial prophylaxis and skin preparation	X	
Epidural analgesia	X	
Opioid-sparing analgesia	X	
Wound catheter and transversus abdominis plane block	X	
Minimal invasive surgery		X
Nausea and vomiting prophylaxis	X	
Avoiding hypothermia	X	
Nasogastric intubation		X
Goal-directed fluid therapy	X	
Perianastomotic drainage	X	
Somatostatin analogues		X
Postoperative multimodal analgesia	X	
Postoperative glycemic control	X	
Urinary drainage early removal	X	
Stimulation of bowel movement		X
Early and scheduled mobilization	X	
Audit	X	

### Patient eligibility

Adult patients (age ≥ 18 and < 90 years of age) scheduled for elective open pancreatoduodenectomy for any periampullary or pancreatic cancer.

### Inclusion criteria

- Patients must be willing to participate in the study and able to provide written informed consent form prior to any study activity.- Preoperative normal renal function, blood electrolytes (sodium, potassium, chlorite) and coagulation tests (PT, PTT).

### Exclusion criteria

- American Society of Anesthesiologists (ASA) physical status classification >3- Preoperative severe malnutrition (Weight loss >15% with respect to usual weight in the last 6 months, according to the new GLIM criteria) (14).- Ascites- Any proven hypersensitivity reaction to parenteral nutrition (PN) components- Palliative surgery- Early postoperative administration of enteral nutrition *via* a naso-enteric or jejunostomy feeding tube placed during surgery.

### Screening and randomization processes

After being screened for inclusion and exclusion criteria, patients or their legal representative will be asked to sign a written informed consent. After enrolment in the study, patients will be randomly allocated into two arms. All reasons for exclusion after screening will be recorded.

Patients will be randomly allocated to ERAS or ERAS plus PN at 8:00 PM of the day of surgery, or at 8 AM in the morning of postoperative day one if the operation was concluded after 8 PM. Randomization will be performed by a computed-generated permuted-block sequence. A specific code will be generated for each center to achieve equivalent grouping. The allocation ratio will be 1:1 with a block size of 4. Randomization will be stratified by neoadjuvant chemo- or chemoradiation therapy and center. Randomization will be competitive among centers.

Surgeons and patients will not be blinded to treatment arm. Masking to allocation will be impossible to achieve for the study nature and design.

Patient chart evaluation and data entry for outcome recording will be done by trained assessors (selected in each center) and not directly involved in patient care and thus masked to patient allocation. Clear information on patient allocation will not be released to any hospital personnel with exception of ethical committee members under specific request.

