## Data collection and management

All data will be collected into an electronic database with a double entry to assure consistency of records. In case of missing or implausible data, queries will be mailed to the participating centers to obtain integrations or corrections. Data collectors will be blinded to allocation.

The patient first and last name and date of birth will be omitted according to the Italian legislation on privacy. Subject identification will be carried out only by the randomization code.

All data will be collected into a dedicated excel spreadsheet. This electronic registry will be identical for all centers and each center will have their own dataset. The excel spreadsheet will be protected by a password possessed by the assessor.

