### Case report form

The following baseline patient-related parameters will be recorded:

- Age (years)- Sex- Weight (kg)- Height (m)- Body mass index (kg/m^2^)- Nutritional risk score-2002- Percent of weight loss in the 6 months prior to surgery- Charlson comorbidity index- Diabetes- Jaundice- Biliary stenting- Routine laboratory test (albumin, preabumin, bilirubin, hemoglobin, creatinine, HbA1c, CRP)- Primary disease with indication to surgical resection- ASA score- Neoadjuvant treatments

The following intraoperative parameters and events will be recorded:

- The day of operation- Type of surgical procedure (PPPD, Whipple)- Type of pancreatic anastomosis (gastric, jejunal)- The level of intraoperative contamination (clean; clean-contaminated; contaminated; dirty)- Use of epidural analgesia, TAP block, subfascial catheter- Intraoperative hypothermia (defined as body temperature < 35.5°C for more than 30 min)- Estimated blood loss (mL)- Volume of IV fluid infusion- Intraoperative blood transfusion- Fluid balance (in and out difference)- Duration of operation (minute)- Main pancreatic duct diameter- Pancreas texture (soft, intermediate, hard)- Fistula risk score

After the operation the following parameters and events will be recorded:

- Capillary blood glucose levels (every 6 h for 5 consecutive days)- Any administration of insulin (for blood glucose ≥180 mg/dL)- Occurrence of a complication (90-days)- Type of complication- The complication burden according to CCI (90-day)- The severity of complication according to Clavien-Dindo classification- The need of reoperation, reason and postoperative day- The need of unplanned intensive care treatment and the duration (days)- The day of canalization to gas and stools- The day of resumption of oral feeding- The need and duration of artificial nutrition (for the control arm)- Potential hospital discharge according to predefined criteria- The actual day of hospital discharge- Disease staging- Readmission rate (30-day)- Mortality rate (90-day)

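### Assessor masking rests on a reason that cannot deliver it, and a published fixed block of 4 lets anyone tracking open allocations foresee about one third of them

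*Protocol article*

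**What the plan says.** **Masking.** The trial is open label. Under Screening and randomization processes the article states "Surgeons and patients will not be blinded to treatment arm" and adds that masking cannot be achieved given the design. It then says that chart evaluation and data entry for outcomes "will be done by trained assessors (selected in each center) and not directly involved in patient care and thus masked to patient allocation", and that clear allocation information is withheld from hospital staff. Pre-trial training repeats that outcome assessors are blinded. Data collection and management states "Data collectors will be blinded to allocation".

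**Data items.** The Case report form section lists "The need and duration of artificial nutrition (for the control arm"). Two secondary outcomes are also tied to one arm: daily calories delivered by PN, and unplanned artificial nutrition in controls. Table 2 records drug administration on days 1 to 5.

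**Allocation.** "Randomization will be performed by a computed-generated permuted-block sequence". "The allocation ratio will be 1:1 with a block size of 4". "Randomization will be stratified by neoadjuvant chemo- or chemoradiation therapy and center". Allocation takes place at 8 PM on the day of surgery, or at 8 AM the next morning if the operation ends later. Exclusion criteria include palliative surgery and early enteral feeding through "a naso-enteric or jejunostomy feeding tube placed during surgery".

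**The concern.** The primary endpoint is the 90-day Comprehensive Complication Index (CCI). It is built from every recorded complication and its assigned Clavien-Dindo grade, so it depends on what is recorded and how it is graded. In an open trial, two safeguards protect that endpoint: assessors who do not know the arm, and allocations that nobody can foresee. As written, neither is secured.

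The only reason given for assessor masking is lack of involvement in care, yet the same sentence gives those assessors the chart. If they can read the arm there, grading is effectively open while the trial report would describe it as blinded. If local staff can foresee the next arm, decisions taken before randomisation may depend on it. Either route could move the CCI comparison in either direction.

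**Working it through.** **Step 1. Masking statements set side by side**

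| Statement | Sits against |
|---|---|
| Assessors are masked because they are outside care (Screening and randomization processes) | They evaluate the chart. Treatment-arm patients receive a named PN product plus a daily vitamin vial from day 1 for 5 days (Study intervention) |
| Data collectors are blinded (Data collection and management) | One form item is for controls only (Case report form), and two secondary outcomes are arm-specific. Whoever completes these must know the arm |
| Clear allocation information is withheld from hospital staff (Screening and randomization processes) | Surgeons are unblinded (same section), and PN is given openly on the ward |

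The article describes one dataset per centre, with the password held by the assessor, and mentions no separate unmasked recorder. That the chart shows PN is an inference, but a strong one.

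**Step 2. Predictability of a 1:1 block of 4**

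The article gives no predictability figure to reproduce. A block with two of each arm has 6 equally likely orders. An allocation is certain once one arm is used up in the block.

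| Position | Probability that it is certain | Probability that the best guess is right |
|---|---|---|
| 1 | 0 | 1/2 |
| 2 | 0 | 2/3 |
| 3 | 1/3 | 1/3 × 1 + 2/3 × 1/2 = 2/3 |
| 4 | 1 | 1 |

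- Share certain: (0 + 0 + 1/3 + 1)/4 = 1/3.
- Best-guess success: (1/2 + 2/3 + 2/3 + 1)/4 = 17/24 = 70.8%, against 50% with no knowledge.

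**Step 3. Unfinished blocks at the planned size**

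Inputs are 2 × 120 = 240 patients (Statistical planning) and 5 centres × 2 neoadjuvant levels = 10 strata. The neoadjuvant share (10% to 50%) and the centre sizes (equal or unequal) are assumptions, because the article does not give them. In simulation the certain share averages 31.6%, with a 95% range of about 28% to 35%, and it barely changes across these assumptions. That is about 0.316 × 240 = 76 patients.

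**Step 4. Alternatives**

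| Scheme | Share certain |
|---|---|
| Fixed block of 4 | 33.3% |
| Fixed block of 6 | 25% |
| Fixed block of 8 | 20% |
| Sizes 4 and 6 in random order | about 5.6% |
| Sizes 4, 6 and 8 in random order | about 2% |

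The last two rows are simulated for an observer who knows the set of sizes but not their order. Varying the size removes most certainty but not all guessability: even a fixed block of 8 leaves a best-guess rate of 66.6%.

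**The case against.** **Masking.** The article provides for two independent trained assessors per centre, agreed complication definitions and a third expert for disagreements (Pre-trial training). These limit grading drift and deserve credit, but they do not mask anyone. Controls may also receive PN after a complication (Control arm), so PN in a chart is not conclusive; routine PN from day 1, however, belongs only to the treatment arm. Redaction and page ownership are details that an article may leave to the full protocol, and their absence is not the point. The point is that the stated reason does not produce the stated property and that the statements conflict.

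**Allocation.** Consent precedes surgery, the coordinating centre handles allocation, and reasons for post-screening exclusion are logged. These safeguards leave three main routes: which patients are approached, the order of surgery, and exclusions decided at operation. The feeding-tube exclusion also requires a decision to feed early by that route. Small fixed blocks give closer balance in strata averaging 240/10 = 24 patients, which is a real advantage.

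**Stronger readings that the documents do not support.**
- A reader might infer that glucose and insulin entries reveal the arm. The insulin rule is common to both arms, and the glucose schedule is listed without restriction to one arm.
- A reader might infer that the assessors themselves fill the control-only field. The article does not say who completes each field; the conflict is with its general statement about data collectors.
- A reader might take one third of allocations as known to everyone. The figure holds only for someone who knows the stratum, the block size and the earlier allocations, and it is an expected share.
- A reader might infer that no PN beyond day 5 is recorded in the treatment arm. The PN-calorie outcome has no day limit. Only a switch to tube feeding lacks an explicit item there.
- A reader might want a bias in CCI points. The documents give no basis for one, and death and reoperation are less exposed to unmasked grading.

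**Conclusion.** The point holds in two parts.

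First, blinded assessment is claimed but not delivered as written. The reason given does not imply masking, and the blinding and non-disclosure statements conflict with arm-specific data items and open-label PN. This rests on the strong inference that charts show routine PN from day 1.

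Second, the fixed, published block of 4 lets anyone who tracks open allocations within a stratum know one third of allocations in advance (about 32% at 240 patients) and guess correctly 71% of the time. Open treatment and stratification by centre make such tracking realistic for local staff, although the article does not show that anyone does it.

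Both are opportunities for bias, without evidence of its occurrence, direction or size. They should be corrected because the remedies are cheap; they do not invalidate the design.

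**What to change.** **Assessment.** Let unmasked site staff complete the treatment and nutrition pages. Record need, route and duration of artificial nutrition identically in both arms. Let the existing assessors and third expert grade complications from extracts without nutrition and infusion entries. If charts cannot be redacted, withdraw the claim of blinded assessment and describe grading as open, with dual assessment and adjudication. Reword the statement that allocation is withheld from hospital staff so that it fits open-label delivery.

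**Allocation.** For remaining patients, generate lists with randomly varying block sizes (for example 4, 6 and 8), and keep sizes and order from the centres. This lowers the certain share from 33% to about 2%.

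**Cost.** The case report form must be laid out again, existing staff take on some redaction work, the new list may need notification to the authority and ethics committees, and possible imbalance within strata grows slightly. Treatment, endpoint and sample size stay as they are.

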### Study duration and definition of termination

The expected duration of enrolment is approximately 2 years.

The study will be considered as terminated when the last enrolled patient will have completed the 90-day follow-up after the date of surgery.

### Study intervention

Patients randomized in the treatment arm will be treated with a full ERAS protocol that establishes oral food “at will” plus parenteral nutrition (PN) from postoperative day 1. A ready-to-use, all-in-one, 3-bag compartment peripheral parenteral solution (mOsm <800) (Olimel N4E®, Baxter Italia, SpA) containing carbohydrate, lipids and proteins will be infused to deliver 20/25 total Kcal/kg/day for a total of 5 days after the operation with the addition of I.V. supplementation of vitamins (one vial/day) (Cernevit®, Baxter Italia SpA).

In case of occurrence of any complication impairing the full or partial recovery of oral food, the treatment will be continued or switched to tube enteral feeding until clinically indicated.

Administration of parenteral nutrition will be through a peripheral vein with a rate of delivery that is calculated based on patient body weight. The total volume of parenteral nutrition will be the result of the calculation of the amount of prescribed calories, multiplied for the patient body weight.

